Few studies have evaluated the impact of sending SMS reminders to participants in CRC screening programs that use FIT kit.[10] A study in the UK did not observe an overall increase in participation, but sending an SMS reminder did increase the number of first-time participants.[11] Studies in Israel observed increased participation among the population of lower socioeconomic status.[12,13] Adherence to (continued participation in) the CRC screening program of the ICO is very high (≥85%); therefore, it would be important to increase participation in people who are invited for the first time and/or those in younger age groups because this could improve the effectiveness of the program (population-wide impact on health). Further, if more people in socially depressed populations participated, health inequity would be reduced by improving accessibility to the CRC screening program.

Our group has conducted a pilot study of sending SMS reminders to test the viability of the intervention in two primary healthcare areas (unpublished data). In our program, people interested in participating in CRC screening have to go to a pharmacy to pick up and return their FIT kit. The pilot study has shown that it is feasible to send SMS reminders for the screening invitation. The preliminary results show that SMS is equal to or better than reminder letters in garnering participation. Phone calls were made to 150 people who had been sent the SMS to assess their understanding of the text message. Eighty percent of the users were aware of having received the message, and of these, 91% correctly identified the purpose of the message. Given the difficulty of implementing interventions that significantly increase participation in CRC screening and given the goal of keeping costs low (each and every health action must not only be evaluated in terms of health impact but in economic terms), it would be useful to identify population subgroups with greater motivation to participate in the program. Once these are identified, specific interventions should be designed and implemented for them. We have identified that in a period of two years (2017-2018), 13,000 FIT kits were collected in the collaborating pharmacies of the program that were not delivered for analysis. It can be assumed that these people are motivated for change (preparation phase), and a small SMS reminder to deliver the test could affect participation. [14.15]

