Cluster randomized controlled trial. Men and women between 50 and 69 years of age from eight primary healthcare areas will be invited to CRC screening. Invitations to the program will be sent weekly. The invitation weeks (clusters) will be randomized so that there will be weeks in which the individuals whose mobile phones we have registered will receive the reminder by letter, and other weeks they will receive the reminder by SMS. The rest of the individuals, for whom we do not have mobile phone information (15%), will receive the reminder by letter as usual. These individuals will not enter the analysis that will compare the letter and the SMS as a reminder. The reminder will be sent to individuals who have not completed the FIT kit 6 weeks into their screening episode, corresponding to approximately 70% of the cases.

Variables

The dependent variable will be participation in screening (yes/no). This variable will be collected prospectively after participants are invited to the screening program through a database connected to the screening program registry. Participation will be analyzed from week 18 after mailing out the invitation letter (week 0). The independent variables that will be collected are the type of reminder (SMS/letter), previous screening status (first-time invited, nonparticipants, participants in the previous round), and socio-demographic variables such as age, sex, and the socioeconomic deprivation index developed by the Agency for Health Quality and Assessment of Catalonia (AQuAS). It is an aggregate index by primary healthcare area that includes the following variables: percentage of manual laborers, percentage of people with insufficient education, and premature mortality in individuals <75 years, avoidable hospitalization rate and population served in primary care). Values range from 0-100, with higher values implying lower socioeconomic levels.

Finally, a variable will be calculated on the accessibility of postal mail (easy access areas/hard to reach areas). This variable will be calculated considering the population growth in the last 10 years and the proportion of municipalities with less than 15,000 inhabitants. Vidal et al, 2014

Sample size

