The sample size (n=10,415) has been calculated to identify differences according to previous screening of 3%. The distribution of our study population by screening is: 14% new invitees, 53% non-participants and 33% participants in the previous round. An alpha risk of 5% and a statistical power of 80% have been considered. In addition, 10% of wrong registered phones have been estimated.

Data analysis

A multivariate analysis will be performed using a logistic regression model with random intercept to compare the experimental intervention (SMS) versus the standard intervention (letter). The "invitation week" will be included in the model to account for cluster variability. Odds ratios and 95% confidence intervals will be calculated.

Intervention 2: SMS for FIT delivery in CRC screening

Study design and population

Cluster randomized controlled trial on all individuals with a mobile phone number registered who have picked up a FIT kit and has not been returned at the pharmacy within 14 days from pick-up. This 14-day time interval has been considered since 90% of the people deliver the screening test within this period and to avoid, moreover, that they have misplaced it. The duration of the study will be 12 months.

Sample size

The basic health areas invited in one year (n=47) will be randomly assigned to the two groups: 1) Experimental group in which an SMS reminder for delivery of FIT will be designed and implemented; 2) This study will have a statistical power of 92% to detect differences in participation of 3% between the experimental group and the control group.

Variables

The dependent variable will be the participation in CRC screening. Participation will be analyzed at 8 week after sending the invitation letter (week 0). The independent variables will be: Intervention (SMS/no intervention), previous screening behavior (new participants, non-participants, participants in the previous round) and socio-demographic variables: age, sex and the socio-economic deprivation index (AQUAS).

Data analysis

A multivariate analysis will be performed using a random intercept logistic regression model to compare the control group (SMS reminder of FIT delivery) and the control group (no intervention). The core health area will be included as a random effects intercept. Odds ratios and 95% confidence intervals will be calculated.

Intervention 3: Screening invitation for successive participants in BC screening

Design and Study population

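### Intervention 2 randomises 47 areas with no balancing factor stated and no area-level baseline of the outcome in the model; a previous-round return figure is probably obtainable and could recover some power cheaply

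*Protocol*

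**What the plan says.** Under Intervention 2, Sample size, the allocation is described in one clause: "The basic health areas invited in one year (n=47) will be randomly assigned to the two groups". The same paragraph gives the power: "This study will have a statistical power of 92% to detect differences in participation of 3% between the experimental group and the control group". It states no allocation ratio, ICC, number of individuals or control rate.

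Under Intervention 2, Variables, the independent variables are the intervention, each person's previous screening behaviour, and "socio-demographic variables: age, sex and the socio-economic deprivation index (AQUAS"). The Variables section of Intervention 1 describes the deprivation index: "It is an aggregate index by primary healthcare area". It is therefore measured at area level, but it is built from deprivation and health-service components and not from kit return.

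Under Intervention 2, Data analysis, the model is a random-intercept logistic regression: "The core health area will be included as a random effects intercept".

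The Background on the colorectal programme says that screening is biennial and that invitations go out by Primary Healthcare Area. It also reports that over 2017-2018 "13,000 FIT kits were collected in the collaborating pharmacies of the program that were not delivered for analysis".

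**The concern.** The independent units are 47 areas, about 23 against 24. Variation between areas in the underlying return rate is the part of the error that more people per area cannot reduce, and the planned random intercept shows that such variation is expected. If areas that returned kits poorly in the last round tend to do so again, the earlier figure predicts the outcome and is available before allocation. If it is not used, that persistent variation stays in the error term, apart from whatever the listed covariates absorb, and chance can give the two arms different underlying return rates. The target effect is only 3 points, so moderate imbalance matters.

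The allocation half of the remedy is available only before randomisation. An analysis plan can add a covariate later, but it cannot add strata to an allocation already made.

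**Working it through.** **Inputs.**
- Areas: 47 (protocol); a 23/24 split is assumed.
- Effect: 3 points (protocol), read as an absolute difference.
- People: 13,000 undelivered kits over two years (Background) and a mobile number for just over 85% (Limitations) give 13,000/2 × 0.85 = 5,525, or 5,525/47 = 117.6 per area. This is a rough proxy. It counts kits never returned, whereas eligibility is not returned at 14 days, so the real pool may be larger.
- Control return of 13%, hence 16% with SMS: assumed.
- Two-sided 5%: assumed; the protocol states a 5% alpha for Intervention 1 only.
- ICC 0.002 to 0.02 and between-round correlation r of 0.5 to 0.9: assumed.

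**1. The stated 92%.** It can be neither reproduced nor refuted, because its inputs are not given. Calculations that ignore clustering come near it for several assumed pairs: 94% with 6,500 people and a 12% control rate, 90% with 6,500 and 15%, 92% with 11,050 and 30%. The point below does not depend on it.

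**2. Chance imbalance.** Between-area SD = √(ICC × p(1−p)). SD of the arm difference = that SD × √(1/23 + 1/24) = that SD × 0.292.
- ICC 0.01: √(0.01 × 0.13 × 0.87) = 3.36 points; × 0.292 = 0.98 points. An imbalance of at least 1.5 points, half the target effect, occurs in 12.6% of allocations.
- ICC 0.02: 4.76 points; × 0.292 = 1.39 points; 28.0% of allocations.

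**3. Power with and without the area figure.** The observed past rate of an area is itself noisy, so its value is discounted:
- reliability = m × ICC / (1 + (m − 1) × ICC), with m = 117.6;
- R² = r² × reliability;
- design effect = 1 + (m − 1) × ICC × (1 − R²).

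The unclustered standard error is √(0.16 × 0.84/2,704 + 0.13 × 0.87/2,821) = 0.95 points, and is multiplied by the square root of the design effect. Power comes from the noncentral t with 45 df, or 44 df with the covariate.

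Example at ICC 0.01 and r = 0.7: reliability = 1.176/2.166 = 0.54; R² = 0.49 × 0.543 = 0.27; the design effect falls from 2.17 to 1 + 1.166 × 0.734 = 1.86; power rises from 55.8% to 62.3%.

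| ICC | Reliability | Power without | Power with, r = 0.5 / 0.7 / 0.9 | Gain (points) |
|---|---|---|---|---|
| 0.002 | 0.19 | 79.7% | 80.0 / 80.3 / 80.8% | 0.3 to 1.1 |
| 0.005 | 0.37 | 69.2% | 70.7 / 72.2 / 74.2% | 1.5 to 5.0 |
| 0.01 | 0.54 | 55.8% | 58.9 / 62.3 / 67.3% | 3.1 to 11.5 |
| 0.02 | 0.71 | 39.7% | 44.1 / 49.6 / 59.1% | 4.5 to 19.5 |

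**4. Cross-checks.** Simulated trials with unequal area sizes at r = 0.7 gave 55.5% to 59.3% at ICC 0.01 and 39.8% to 46.7% at ICC 0.02: the same direction, with gains about 3 points smaller than in the table. With 6,500 people and a 20% control rate, r from 0.5 to 0.9 takes power from 46% to 50-59% at ICC 0.01 and from 32% to 36-51% at ICC 0.02.

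Both the table and the simulation compare with a model that has no covariates. The protocol's model already contains the deprivation index and the individual variables.

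**The case against.** **Silence is not a choice.** A reader might infer that the protocol prescribes unrestricted randomisation here. It does not. It says only that the areas are assigned at random, and the term simple random allocation is used for Intervention 3 alone. This stands: the supportable statement is that no balancing factor is given.

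**The per-area record is not documented.** The protocol reports one programme-wide count. That each area's return figure exists is an inference from area-based invitation and from the fact that undelivered kits have been counted. It is a reasonable inference, but still an inference. That the past figure would be the best available predictor is likewise unsupported by the document.

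**Other covariates may already do part of the work.** The deprivation index and individual screening history may absorb some between-area variation, so the gains above are probably too large by an unknown amount. This stands. It does not remove the point: neither variable measures whether people in an area who already hold a kit tend to return it.

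**The gain may be small.** At ICC 0.002 or below it is negligible, and the largest figures require a correlation of 0.9. This stands.

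**Validity is not at issue.** A reader might infer that the treatment comparison is biased or that the 92% is wrong. Neither follows. Randomisation with a random intercept for area gives valid inference, and chance imbalance is reflected in the interval. The 92% cannot be tested without its inputs.

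**Covariates can be left to an analysis plan.** True of the model term, but not of stratified or paired allocation.

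**Conclusion.** The point holds as a cheap design improvement and not as an error in the protocol. Intervention 2 states no balancing factor for its 47 areas and lists covariates without an area-level baseline of the outcome, while the programme's structure makes such a baseline very probably obtainable before allocation.

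The benefit depends on quantities that the protocol does not give. Under the assumed inputs, and before allowing for the covariates already planned, it is near nil at ICC 0.002 or less and becomes useful from about ICC 0.01: 3 to 12 points there and 4 to 20 points at ICC 0.02. If the ICC is of that order, an imbalance of at least half the target effect would arise in roughly one allocation in eight (ICC 0.01) to more than one in four (ICC 0.02).

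**What to change.** 1. Before allocation, tabulate for each of the 47 areas, from the previous round, the share of kits outstanding at day 14 that were later returned. If this cannot be extracted, the share of collected kits never returned is a weaker substitute. Its denominator is all collected kits, and the protocol says 90% of people deliver within 14 days, so it largely describes a different group from the trial population.
2. Stratify the areas into two or three levels of that figure, or pair them on it, and randomise within strata or pairs. Pairing 47 areas leaves one unpaired, so stratification is simpler. State the method in the protocol.
3. Add the figure as a fixed area-level covariate in the random-intercept logistic model, next to the deprivation index.

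The cost is one registry query before randomisation, one sentence in the protocol and 1 degree of freedom at area level (44 instead of 45 in the calculation above). If the query shows that the figure cannot be produced by area, little has been spent and the planned analysis remains valid.

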Healthcare financer perspective will be analyzed. Following healthcare costs will be included, which will be evaluated in the population-based screening programs: a) Labor costs, consumables and depreciation of property, facilities and equipment, as well as "overheads". The SMS alternative will specifically include the personnel and infrastructure fixed costs; b) Diagnosis costs, specifically the costs of evaluating cases with a positive screening test. Future costs will not be included.

The effectiveness will be measured through the number of people who have participated in the screening and, if applicable, the proportion of advanced malignancies detected by increased participation will be calculated.

The result will be specified as an incremental ratio between costs and effectiveness (ICER) which was defined as cost per participants. The temporary period of analysis will be 1 year. A deterministic sensibility analysis will be applied to test the robustness of the results.

LIMITATIONS

Among the limitations of the study, we highlight that in order to incorporate SMS as a new communication tool; the proportion of users with a correct number must be high. We are able to access the mobile phone number of more than 85% of the eligible population and this proportion is increasing year after year.

In addition, in two previous studies that we carried out in both BC and CRC cancer screening, the proportion of wrong numbers was 9-10%.

The size of the SMS might be a limitation, as it has to be limited to 160 characters. However, we can add a link to more detailed information on the screening process. Example: ICO reminds you of the importance of preventing RCC. If you want to take the test, go to: <https://zmz.es/dKmBlg>

Ethical aspects

The Catalan Institute of Oncology the entity responsible for the processing of personal data of men and women between 50 and 69 years of age in the southern metropolitan area of Barcelona invited to participate in population programs for the early detection of cancer, is in the process of adjusting and updating its protocols, arrangements, conventions, terms, ..., to respond adequately to new regulations on confidentiality and protection of personal data (Regulation 2016/679 of the European Parliament and Council of 27 April 2016 on the protection of individuals (RGPD) and Law Organic Law 3/2018 of 5 December on the Protection of Personal Data and Guarantee of Digital Rights (LOPD-GDD).

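### Intervention 2 claims 92% power for 47 randomised areas without the inputs behind it, and at the protocol's own kit volumes 92% survives only if between-area clustering is very small or the control return rate very low

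*Protocol*

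**What the plan says.** Under Intervention 2, the Protocol describes a "Cluster randomized controlled trial on all individuals with a mobile phone number registered who have picked up a FIT kit" and who has not returned it within 14 days. It adds: "The duration of the study will be 12 months". The sample-size paragraph says "The basic health areas invited in one year (n=47) will be randomly assigned to the two groups", and then: "This study will have a statistical power of 92% to detect differences in participation of 3% between the experimental group and the control group". The data-analysis paragraph plans a logistic model with a random intercept for health area.

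That is all the sample-size information for this trial. It has no number of individuals, control-arm return rate, alpha, ICC or design effect, and does not say whether 3% is absolute or relative. The only alpha in the document belongs to Intervention 1: "An alpha risk of 5% and a statistical power of 80% have been considered".

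Two figures elsewhere bear on the volume. The Background says that over 2017–2018 "13,000 FIT kits were collected in the collaborating pharmacies of the program that were not delivered for analysis". The Limitations say "We are able to access the mobile phone number of more than 85% of the eligible population".

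**The concern.** When whole areas are randomised, people in the same area are not independent evidence. Power then depends on the number of areas and the ICC as well as on the number of people. The analysis plan accepts this by fitting an area random intercept, but the power statement shows no matching allowance.

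The Protocol itself publishes the 92%, so this is more than detail left to a later analysis plan. Readers will rely on the figure if the result is null: with 92% power, a null result suggests that a 3-point gain is unlikely, and with about 50% power it says little. The same participation result also feeds the cost-effectiveness analysis.

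**Working it through.** **1. Trying to reproduce 92%.** The comparison is of two proportions, p and p + 0.03, with equal arms and two-sided alpha 0.05 (assumed). Without clustering, several pairs give about 92%:

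- N = 5,525 with a control rate of 11%
- N = 6,500 with 14%
- N = 11,050 with 30%
- N = 13,000 with 50% (93%)

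A cluster-adjusted formula can also give about 92%: N = 11,050 at 10% with ICC 0.005, or N = 13,000 at 15% with ICC about 0.003. The stated figure therefore does not identify its formula or its inputs.

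**2. Tying N to the Protocol's volume.** N and the control rate are linked. Without a reminder, the eligible people who never return a kit should number about as many as the undelivered kits.

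- Undelivered kits per year: 13,000 / 2 = 6,500.
- With a registered mobile: 6,500 × 0.85 = 5,525. Because the Protocol says more than 85%, I use 5,525 to 6,500.
- So N × (1 − p) = V, that is N = V / (1 − p), with V between 5,525 and 6,500.

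The two cluster-adjusted pairs in step 1 do not fit this. They imply 11,050 × 0.90 = 9,945 and 13,000 × 0.85 = 11,050 non-returners a year, roughly 1.5 to 2 times the documented volume.

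**3. Formula.** People per area m = N / 47. Design effect DE = 1 + (m − 1) × ICC. SE = √(DE × [p(1 − p) + (p + 0.03)(0.97 − p)] / (N/2)). Power = Φ(0.03/SE − 1.96).

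Example with p = 20% and V = 5,525:

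- N = 5,525 / 0.80 = 6,906, and m = 146.9.
- The variance sum is 0.1600 + 0.1771 = 0.3371.
- ICC 0: SE = √(0.3371 / 3,453) = 0.00988; Φ(3.036 − 1.96) = 85.9%.
- ICC 0.005: DE = 1.73, SE = 0.01299; power 63.6%.
- ICC 0.01: DE = 2.46, SE = 0.01549; power 49.0%.

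**4. Power (%) over the range, for V = 5,525 / V = 6,500.** The ICC values are assumptions.

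| Control rate | N | ICC 0 | 0.001 | 0.005 | 0.01 |
|---|---|---|---|---|---|
| 5% | 5,816 / 6,842 | 99.6 / 99.9 | 99.2 / 99.7 | 95.5 / 97.0 | 87.6 / 89.7 |
| 10% | 6,139 / 7,222 | 95.8 / 97.9 | 93.4 / 96.1 | 81.9 / 85.4 | 68.2 / 71.1 |
| 20% | 6,906 / 8,125 | 85.9 / 90.9 | 81.0 / 86.0 | 63.6 / 67.6 | 49.0 / 51.5 |
| 30% | 7,893 / 9,286 | 81.9 / 87.6 | 75.7 / 81.2 | 56.3 / 59.9 | 42.0 / 44.0 |
| 40% | 9,208 / 10,833 | 83.2 / 88.7 | 76.2 / 81.6 | 54.8 / 58.1 | 39.8 / 41.5 |
| 50% | 11,050 / 13,000 | 88.4 / 92.8 | 81.1 / 85.8 | 57.2 / 60.3 | 40.8 / 42.3 |
| 70% | 18,417 / 21,667 | 99.5 / 99.8 | 96.9 / 98.2 | 74.7 / 76.9 | 53.1 / 54.3 |

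**5. Largest ICC at which 92% still holds.**

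- Control rate 10%: 0.0016 / 0.0027.
- Control rate 70%: 0.0020 / 0.0024.
- Control rates of 20% to 40%: 92% is not reached even with ICC 0. At 50% it is missed with V = 5,525 and barely met with V = 6,500.
- Control rate 5%: 0.0074 / 0.0086.

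**6. More people per area would not solve it.** With unlimited people in 47 areas and ICC 0.01, power is at most 90% at a 10% control rate, 71% at 20%, 60% at 30% and 54% at 50%.

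These figures assume equal area sizes and a normal reference. A t reference with 45 degrees of freedom takes off a further 1–2 points, and unequal area sizes lower power again.

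**The case against.** A reader might infer that the 92% came from a formula for individual randomisation. The documents do not support that. N, control rate and alpha are all missing, and pairing a volume with whatever control rate yields 92% is fitting backwards. Silence about an ICC does not prove that clustering was ignored.

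A reader might also infer that ordinary variation between areas must push power far below 92%. The documents give no ICC, least of all for people already past day 14. Starting from an unadjusted 92% with 118 people per area (5,525 / 47), an ICC of 0.001 costs only 3 points, to 89%. The listed covariates, previous screening behaviour and the area deprivation index, may also absorb some of the variation.

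Both objections stand, and they limit the point to what is stated here. They do not rescue the 92%. The cluster-adjusted combinations that reach it need more non-returners than the Protocol reports. The volume tie has its own weakness: it treats an undelivered kit as non-participation and takes 2017–2018 as typical. Kits returned after the 8-week assessment would loosen it.

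**Conclusion.** The point holds in this form: the 92% cannot be checked, nothing shows that it allows for clustering, and at the Protocol's own volumes it holds only under narrow conditions. For control rates of 10–70% those conditions are an ICC of about 0.003 or less, and for much of the middle of that range no ICC is small enough. At a control rate of about 5%, an ICC below about 0.007–0.009 would do.

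Across control rates of 10–70%, power is 82% to over 99% without clustering, about 55–85% at ICC 0.005 and about 40–71% at ICC 0.01. This rests on four assumptions: 3% means percentage points, alpha is two-sided 5%, N follows from 5,525–6,500 non-returners a year, and the ICC lies in the range shown. No arithmetic error in the 92% has been demonstrated. What is shown is that the design supports the figure only with very little clustering or a very low control rate.

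**What to change.** Replace the 92% sentence with the power for 47 clusters (23 versus 24). State the expected eligible people per area, the control-arm return rate among people past day 14, the alpha and its sidedness, whether 3% is absolute, and an ICC with a range. Estimate the control rate and the ICC by area from the 2017–2018 programme data. Do not claim 92% unless that calculation supports it.

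Add each area's earlier kit-return proportion as a cluster-level covariate in the planned random-intercept model, to recover some precision. Stratifying the allocation on the same proportion is optional.

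The cost is one recalculation from programme data and a change of wording. The stated power will probably fall. No extra participants are needed.

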**TITLE: Implementation of Text Messaging (SMS) as an Improvement Tool in Population-based Cancer Screening Programs**

Principal Investigator: [name]

ABSTRACT

The aim of this project is to assess the impact on health and economics of the implementation of text messaging (SMS) in cancer screening programs. Three interventions with SMS will be evaluated through community trials. In the colorectal cancer screening program the following interventions will be tested: a) Participation reminder: six weeks after sending the invitation letter of the colorectal cancer program and if there has not been a response, a reminder SMS will be sent in front of the usual method by letter; b) Reminder to return the fecal occult blood test: SMS reminder of test delivery versus no intervention. This reminder will be sent to the individuals who have gone to the pharmacy to pick up a fecal occult blood test and they have not returned it after 14 days. The impact on participation will be analyzed and, if applicable, the proportion of advanced neoplasm will be calculated by increase in participation. In the breast cancer screening program, the invitation by SMS versus the usual invitation by letter will be studied in women who had participated in the previous screening round. The impact on participation will be analyzed. A cost-effectiveness analysis of the three interventions will be carried out. The incremental cost ratio of the interventions between cost variation and effectiveness variation will be calculated.

BACKGROUND/ STATE OF THE ART

Purpose of the project

Cancer screening programs base their benefit on identifying a specific disease in an asymptomatic phase. For this purpose, they use some test to screen which individuals have a higher probability of having the disease. Currently, eligible population is invited to participate in those programs by mail. In recent decades, technologies of information and communication have been introduced into everyday life [1]. E-mail and mobile phone have been established as the main channels of communication of many people, displacing traditional postal mail or landline phone.

The field of health has been no exception to this reality, health systems are in a period of transition towards a Networked Society [2-4].

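### Intervention 2 reads its outcome 8 weeks after the invitation letter, although people enter 14 days after kit pick-up, so those who collect from week 6 on cannot count as participants in either arm

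*Protocol*

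**What the plan says.** **Entry.** Protocol, Intervention 2, Study design and population, takes people with a registered mobile number "who have picked up a FIT kit and has not been returned at the pharmacy within 14 days from pick-up". The Abstract gives the same trigger for the SMS itself: it goes to those who "pick up a fecal occult blood test and they have not returned it after 14 days". Entry is therefore an individual date, pick-up plus 14 days.

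**Outcome.** Protocol, Intervention 2, Variables, makes participation in CRC screening the dependent variable and fixes when it is read: "Participation will be analyzed at 8 week after sending the invitation letter (week 0", counted from the letter and not from pick-up or eligibility.

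**The programme around it.** Under Background, "people interested in participating in CRC screening have to go to a pharmacy to pick up and return their FIT kit". No latest pick-up date appears anywhere. Intervention 1, Design and study population, describes a reminder at week 6 for "individuals who have not completed the FIT kit 6 weeks into their screening episode, corresponding to approximately 70% of the cases"; the Abstract calls the letter version of this reminder the usual method. For Intervention 1 the outcome timing is "Participation will be analyzed from week 18 after mailing out the invitation letter (week 0".

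**Power.** Intervention 2, Sample size: "This study will have a statistical power of 92% to detect differences in participation of 3% between the experimental group and the control group".

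**The concern.** The entry clock starts at pick-up and the outcome clock starts at the letter, and nothing ties the two together. A person can qualify for the trial on or after the day on which the outcome is read. By the entry rule that person had not returned the kit, so the week-8 record is a non-participation that no text message could have prevented. Others qualify just before the cut-off and give the message very little time.

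This is the only dependent variable stated for Intervention 2. If many of those enrolled cannot respond by definition, a null result could not be read: an ineffective SMS and an SMS sent too late to be counted would look alike. The protocol fixes this time point itself, so it is not a detail left for an analysis plan to supply.

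**Working it through.** **Step 1: timing.** Entry week (and SMS week in the SMS arm) = pick-up week + 2. Time left = cut-off week - (pick-up week + 2).

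| Pick-up week | Entry week | Weeks left to week 8 | Weeks left to week 18 |
|---|---|---|---|
| 0 | 2 | 6 | 16 |
| 2 | 4 | 4 | 14 |
| 4 | 6 | 2 | 12 |
| 5 | 7 | 1 | 11 |
| 6 | 8 | 0 | 10 |
| 7 | 9 | -1 | 9 |
| 8 | 10 | -2 | 8 |
| 16 | 18 | -10 | 0 |

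From pick-up week 6 on, the week-8 outcome of an eligible person is fixed as non-participation in both arms. The one edge case is a week-6 collector who returns the kit on the cut-off day itself.

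**Step 2: are such pick-ups to be expected?** Yes. The programme prompts about 70% of invitees at week 6, and Intervention 1 treats screening episodes as still running at week 18. How many of those enrolled in Intervention 2 collect this late is not stated.

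**Step 3: the stated 92%.** It cannot be reproduced. The protocol gives 47 areas and a 3% difference, but no number of individuals, control return rate or intracluster correlation for this trial. As an illustration, take the 13,000 unreturned kits in two years and 85% mobile coverage: 13,000/2 x 0.85 = 5,525 people. Without clustering and with two-sided alpha 5%, a 3-point difference then has 94% power at a control rate of 10%, 85% at 15%, 67% at 30% and 61% at 50%. Below, 92% is used only as a nominal starting point.

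**Step 4: dilution.** Let f be the share of enrolled people who collect at week 6 or later (an assumption). A 3-point difference among the rest becomes 3 x (1 - f) overall. Power is computed in two ways, both without clustering:
- Constant variance: Phi((1 - f)(1.960 + 1.405) - 1.960).
- Binomial variance: take the n per arm that gives 92% for b versus b + 0.03 (4,245 at b = 20%, 5,428 at 30%, 6,283 at 50%), then recompute power for (1 - f)b versus (1 - f)(b + 0.03).

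| f (assumed) | Overall difference | Constant variance | b = 20% | b = 30% | b = 50% |
|---|---|---|---|---|---|
| 10% | 2.7 points | 85.7% | 88.3% | 87.7% | 85.9% |
| 20% | 2.4 points | 76.8% | 83.4% | 82.1% | 78.0% |
| 30% | 2.1 points | 65.4% | 77.2% | 75.1% | 68.8% |

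**Step 5: the odds ratio.** The loss shows mainly on the difference scale, on which the protocol states its target. Fixed non-participants in both arms leave the ratio of proportions unchanged, so the planned odds ratio moves less. At b = 30% it is (0.33 x 0.70)/(0.67 x 0.30) = 1.15; with f = 30% it is (0.231 x 0.79)/(0.769 x 0.21) = 1.13. The loss of power remains.

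**The case against.** **The 8 may be a slip.** The sentence closely parallels the week-18 sentence of Intervention 1, and Intervention 3 also uses 8 weeks, so a digit may have been dropped or a figure carried over. This is plausible, but nothing in the protocol settles it, and on any of these accounts the sentence has to change.

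**Randomisation protects the comparison.** This stands. Areas are randomised, pick-up precedes the SMS, and both arms share one clock, so pick-up timing is balanced in expectation. A reader might infer that the trial would be confounded by how early people collect their kits, or could show a spurious SMS benefit; the documents support neither. For a superiority question the error is conservative.

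**The size is unknown.** This also stands. A reader might combine the roughly 30% who have completed by week 6 with the 45% participation benchmark and infer that up to a third of the trial, (45 - 30)/45, is affected. That does not follow. The ratio concerns completions among all invitees and uses a European standard that the programme does not reach. The trial enrols only people who miss the 14-day mark (the protocol says 90% return within it), and completions after week 6 include people who collected before week 6. It says nothing about f. Nor should the constant-variance column be taken as the expected power; it is the floor of the range.

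**The 3% may already be the difference on the stated endpoint.** Then the 92% needs no discount, but the difference required among those able to respond rises to 3/(1 - f): 3.3 points at f = 10% and 4.3 at f = 30%.

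**Conclusion.** The point holds on the protocol's own dates. As written, an eligible person who collects at week 6 or later is a non-participant in either arm by construction, and one who collects in weeks 4 to 6 leaves the SMS no more than 2 weeks. The consequence is dilution toward no difference and lower power. The timing conclusion needs no assumption beyond the stated 14 days and 8 weeks. The size does: f is not in the protocol, and the illustrative range (2.7 points and 86-88% power at f = 10%; 2.1 points and 65-77% at f = 30%) assumes a true 3-point difference among the rest, a nominal 92% that cannot be checked, control rates of 20-50% and no clustering. The shorter windows of the week 4 to 6 collectors are not included in these figures.

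**What to change.** Replace the outcome sentence of Intervention 2 so that participation means a FIT kit returned within a fixed window from the day-14 eligibility date, for example 8 weeks, with the same clock in both arms. Every participant then has equal follow-up from the moment the SMS can act.

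Second best is the week-18 time point of Intervention 1. A week-6 collector would then have 10 weeks, but the clock would still start at the letter: follow-up stays unequal, and collectors from week 16 on have no window.

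The cost is one sentence and a somewhat later data lock: 8 weeks after the last eligibility date under the preferred option, or up to about ten weeks later than now with week 18 (18 - 8 = 10). No new data are needed, since the 14-day rule already requires pick-up and return dates in both arms.
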